| **Background** | Ten percent of patients with cirrhosis develop ascites. In 90% of patients, ascites can be treated with diuretics. The management of the remaining 10% with diuretic resistant ascites is challenging. Symptoms including abdominal pain, dyspnoea, nausea, vomiting, and anorexia have a detrimental impact on the quality of life. Repeated large volume paracentesis provides only temporary improvement of symptoms. |
| --- | --- |
| **Hypothesis** | Insertion of a tunnelated peritoneal catheter (PleurX) allows repeated intermittent small volume fluid drainage at home. The treatment may improve the management of ascites and have a beneficial effect on the quality of life. |
| **Objectives** | To evaluate the beneficial and harmful effects of the peritoneal catheter (PleurX) versus repeated large volume paracentesis for patients with cirrhosis and diuretic resistant ascites. |
| **Design** | Investigator initiated, randomised, single blind, parallel arm, controlled trial. |
| **Blinding** | Due to the nature of the intervention and the primary outcome measure, we are unable to conduct the trial with blinding of the patients, the investigators or use blinded outcome assessment. |
| **Interventions** | Tunnelated peritoneal (PleurX) catheter versus large volume paracentesis. All patients will receive ciprofloxacin to prevent spontaneous bacterial peritonitis. |
| **Population** | We will include 32 adult patients with cirrhosis of any aetiology and diuretic resistant ascites. |
| **Sites** | Primary site: Gastro Unit, medical division, Hvidovre University Hospital, Denmark,  Gastrounit, medical division, Herlev University Hospital, Denmark, Department of medicine, Gastroenterology, Køge Hospital, Denmark, Department of Gastroenterology and Hepatology, Odense University Hospital, Denmark. |
| **Inclusion period** | 48 months. |
| **Follow up** | The total duration of follow up is six months. |
| **Primary Outcomes** | The primary outcome is paracentesis free survival. |
| **Secondary Outcomes** | Secondary outcomes include cumulative number of paracentesis, cirrhosis-related complications, safety, quality of life, changes in metabolic and biochemical parameters. |

|  | trial flow illustrated in flow chart | | | | | | |  |
| --- | --- | --- | --- | --- | --- | --- | --- | --- |
| **Prior to enrolment** | Identify eligible patients with ascites. Collect informed consent. | | | | | | |  |
|  |  |  |  | | |  |  |  |

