Two investigators will independently assess if patients fulfil all of the inclusion and none of the exclusion criteria. We will attempt to gather data on patients who are excluded from the study and data on patients who are too ill to participate in follow up assessments. We will collaborate with primary health care providers including at-home nurses in order to collect valid information about adverse events and other clinical outcomes.

Subject Withdrawal

Patients may withdraw voluntarily from the study at any time upon request. The investigator can also withdraw patients from the trial if the patient becomes unstable or there are safety concerns. If patients wish to withdraw or are withdrawn from the study, we will attempt to collect data on adverse events and other clinical outcomes based on hospital or health care records.

Premature Termination or Suspension of Study

This study may be suspended or prematurely terminated if there is sufficient reasonable cause. Written notification, documenting the reason for study suspension or termination, will be provided by the suspending or terminating party. Circumstances that may warrant termination include, but are not limited to: Determination of unexpected, significant, or unacceptable risk to subjects.

Randomisation procedure

The allocation sequence will be generated based on simple 1:1 randomisation using computer generated random numbers. The allocation will be concealed in serially numbered opaque sealed envelopes kept at a central independent randomisation office at the Gastro Unit, Hvidovre Hospital by a person not otherwise involved in the trial in order to ensure that the allocation of the next patient is concealed until the moment of randomisation. The office will be contacted by phone by recruiting physicians.

blinding

Due to the nature of the intervention, it is not possible to conduct the trial with blinding of patients or investigators.

TRIAL FLOW

prior to enrolment

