The primary outcome measure is paracentesis free survival. With an estimated probability of paracentesis free survival set to 0.3 at the end of the trial, an allocation ratio of 1:1, alpha 5% and power 80%, the required sample size is estimated to be a total of 28 patients (14 patients in each group). After taking into account the risk of participant dropout the sample size is set to be 32 patients (16 patients in each group).

Statistical analyses

We plan to include all patients randomised (intention to treat) regardless of compliance or follow up. Patient characteristics will be summarised using medians with interquartile range or proportions. Groups will be compared using t-tests or chi-square tests as appropriate. The level of significance will be set to 5%. The primary outcome measure will be evaluated using Kaplan Meier Plots and log-rank tests. Univariate and multivariate logistic regression analysis will be conducted to identify potential predictors of paracentesis free survival.

Handling of data

Data will be retrieved from medical records, information provided by the patients at trial visits as well as laboratory (biochemistry) assessments and investigational results. Data will be collected to Case report forms and entered into an electronic database by the principal investigator. Case report forms from the supporting sites will be sent by secure mail to the principal investigator. The database is anonymous. A trial participant identification list will be stored safely by the principal investigator.

Missing data

During the trial, we plan to search for information about missing data in the medical records. Investigators will pursue the options of repeating biochemistry and blood analyses when this is possible. Invasive procedures will not be repeated, should data be missing after the participant has completed the trial investigations.

Quality Control

The study personnel will be trained and tested in all study related procedures to ensure adequate quality control. In particular, investigators will be tested 0to ensure the optimal use of the interventions assessed (PleurX and large volume paracentesis). All investigators are specialised hepatologists with extensive experience in the management and observation of patients with refractory ascites including experience in the use of the PleurX and large volume paracentesis through their clinical work.

Data registration and rules for the control of investigation procedures

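### Simple 1:1 randomisation of 32 patients does not guarantee the planned 16 per group; the cost in power is modest, but the sample size keeps no reserve for it

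*Protocol*

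**What the plan says.** Under Randomisation procedure, the protocol states: "The allocation sequence will be generated based on simple 1:1 randomisation using computer generated random numbers". The sequence goes into numbered, sealed envelopes at a central office that recruiting physicians telephone. No blocking, stratification, minimisation or fixed arm total is described.

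Under Sample Size Considerations, "the required sample size is estimated to be a total of 28 patients (14 patients in each group"), on the basis of "an allocation ratio of 1:1, alpha 5% and power 80"%. The increase is explained in one way only: "After taking into account the risk of participant dropout", "the sample size is set to be 32 patients (16 patients in each group"). The flow chart in the synopsis also shows 16 patients in each arm.

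The primary analysis is given under Statistical analyses: "The primary outcome measure will be evaluated using Kaplan Meier Plots and log-rank tests".

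**The concern.** The arm sizes are stated as if they were known, but the allocation method leaves them to chance. In a trial of 32 a noticeably uneven split is common. An uneven split carries less information than an even one of the same total, and the extra four patients are already assigned to dropout. At stake is some power and the agreement between two sections of the protocol. The validity of the comparison is not at stake.

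**Working it through.** **Inputs from the protocol.** Total randomised 32, planned 16:16. Required before dropout 28, planned 14:14. Allocation simple 1:1. Alpha 5%, power 80%. Primary test log-rank.

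**Assumptions.** Alpha is two-sided (the protocol does not say). The protocol's own claim that 14:14 gives 80% power is taken as given. The figure of 28 cannot be reproduced, because only one probability is stated ("With an estimated probability of paracentesis free survival set to 0.3 at the end of the trial"), with no comparator rate or hazard ratio. The dropout rate is not stated either; the step from 28 to 32 implies 4/32 = 12.5%.

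**1. Distribution of the split.** Let X be the number allocated to PleurX, X ~ Binomial(32, 0.5).

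- P(16:16) = C(32,16)/2^32 = 601,080,390/4,294,967,296 = 14.0%
- P(either arm below 14) = 2 × P(X ≤ 13) = 2 × 0.1885 = 37.7% (18.9% for one named arm)
- P(smaller arm ≤ 12) = 21.5%
- P(smaller arm ≤ 11) = 11.0%
- P(smaller arm ≤ 10) = 5.0%

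These count patients randomised, before any dropout.

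**2. Information lost.** The effective sample size, meaning the total that an equal split would need for the same information, is N_eff = 4·n1·n2/32. Its mean under simple randomisation is N − 1 = 31.

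**3. Power.** For a log-rank test at a fixed effect and event fraction (Schoenfeld scaling), anchored at 80% for 14:14:

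Power = Φ( √(N_eff/28) × (1.960 + 0.842) − 1.960 ).

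If 4 of 32 are lost in proportion to arm size, N_eff is multiplied by 28/32.

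| Split | N_eff, no dropout | Power | N_eff, 4 lost | Power |
|---|---|---|---|---|
| 16:16 | 32.0 | 85.0% | 28.0 | 80.0% |
| 13:19 | 30.9 | 83.7% | 27.0 | 78.6% |
| 12:20 | 30.0 | 82.6% | 26.3 | 77.4% |
| 11:21 | 28.9 | 81.2% | 25.3 | 75.8% |
| 10:22 | 27.5 | 79.3% | 24.1 | 73.8% |

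Worked example, 13:19 with 4 lost: 4 × 13 × 19/32 = 30.875; × 28/32 = 27.02; √(27.02/28) = 0.982; 0.982 × 2.802 − 1.960 = 0.792; Φ(0.792) = 78.6%.

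Averaged over all splits, power is 83.8% against 85.0% at 16:16 without dropout, and 78.7% against 80.0% with four lost.

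**4. What blocking achieves.** With blocks of 2, 4 and 6, the number allocated before the last block is always even, so an unfinished last block has 2 or 4 places filled at patient 32. Two filled places can at worst go to one arm (2:0). Four filled places of a block of 6 can at worst be 3:1. Either way the arms differ by at most 2, which is 17:15. The same holds for blocks of 4 and 6. At 15:17 power is 84.8% without dropout and 79.8% with four lost.

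**The case against.** The strongest reply is that simple randomisation is a legitimate choice with a real advantage here. The trial is open, so recruiters see past allocations at their own site, and only unrestricted allocation makes those uninformative about the next patient. The log-rank comparison by intention to treat is valid at any split. The stated 16 per group can be read as an expected number. All of this stands, and it keeps the point small.

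A reader might infer from the 38% that the trial has a 38% chance of being too small. The protocol does not support that. It gives 14 as half of a total of 28 and does not call it a minimum for each arm. With 32 randomised, the effective size stays above 28 down to 11:21, so before dropout the chance of falling short is 5%, not 38%.

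A reader might also infer that allocation will drift with calendar time over the 48-month inclusion period. Simple randomisation produces only chance imbalance over time, and the protocol describes no time trend in care or case mix, so that claim is not made here.

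What the reply does not remove is the mismatch between an unrestricted method and stated arm sizes, and the absence of any reserve for imbalance once the dropout allowance is used.

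**Conclusion.** The point holds as a modest design weakness. The method described gives the planned 16:16 with probability 14% and does not guarantee it. On average it costs one patient's worth of information (31 of 32) and a little over one percentage point of power: 85.0% to 83.8% without dropout, 80.0% to 78.7% if the implied allowance of four is used in full. The less favourable splits cost more after dropout: 77.4% at 12:20, with a 21.5% chance of that or worse, and 73.8% at 10:22, with a 5.0% chance of that or worse.

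The probabilities of the splits need only the total of 32 and simple 1:1 allocation. The power figures also rest on the protocol's unreproduced claim of 80% at 14:14, a two-sided test and losses in proportion to arm size. The change is worth making because it is cheap, not because the design as written is invalid.

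**What to change.** Under Randomisation procedure, replace simple randomisation with one central list in permuted blocks of randomly varying size, for example 2, 4 and 6, or 4 and 6 to avoid pairs in which the second allocation is fixed by the first. The independent randomisation office should generate and hold the list, and the block sizes should not be disclosed to recruiters or printed in the protocol that the sites receive. If a list with equal totals is in fact already in use, describe it and correct the word simple.

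The cost is a new computer-generated list and one sentence; the envelopes and telephone procedure stay as they are. The downside is slight predictability in an open trial. Random block sizes limit it, as does central telephone allocation from a single list across four sites, where a recruiter does not routinely see allocations made elsewhere.

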Once the catheter is placed, drainage of ascites can be done using vacuum bottles connected to the catheter (see Appendix F). A home nurse will be trained in the drainage procedure and patient monitoring by specialised company staff from Vingmed. (http://www.carefusion.com/our-products/interventional-specialties/drainage/about-the-pleurx-drainage-system/patient-information-pleurx-system/how-to-drain-at-home). The home nurse will ensure that only a maximum of two litres of ascites fluid is removed at a time.

*Large volume paracentesis*: Removal of more than five litres of ascites is defined as large volume paracentesis. Initially, an abdominal ultrasound is performed. This allows an estimate of the ascites volume and distance from the skin to the ascitic fluid. The procedure is performed with the patient lying on his back in a slightly recumbent position toward the site of paracentesis. The ultrasound is used to ensure adequate insertion of the needle in the ascitic fluid. Generally, the insertion site is inferior to umbilicus 2-3 fingerbreadths below the umbilicus. The area is cleaned with betadine in and sterile drapes applied. Using sterile technique, local anesthesia is applied to the area from the skin to the peritoneum. A small incision is made (about 1.5 cm). Subsequently, the catheter, which contains a needle is inserted. Once fluid is aspirated, the needle is removed from the plastic catheter. The catheter is then attached to the catheter bag. After the procedure, the patient remains in hospital for observation until the fluid is drained. Vital signs are checked and the amount of fluid drained is registered. After removal of 4 liters, 25 cc of albumin (25% solution) is given for every following 3 liters of ascitic fluid removed.

Potential Risks

Risks associated with peritoneal catheter and large volume paracentesis

The risks associated with insertion of a peritoneal catheter and large volume paracentesis include pain at insertion of the drain, ascites leakage, haemorrhage, hypotention, electrolyte depletion, protein depletion, peritonitis, and bowel perforation. Based on previous evidence,^51 53^ the combined risk of these adverse events is 10% in both intervention groups.

*Pain*: Infiltration of the puncture site with a local analgesic will be used before insertion of the peritoneal catheter and large volume paracentesis. The administration of local anaesthetic may be pain free or be associated with a sharp sudden pain.

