Collection of blood tests for standard biochemical analysis, measurement of weight and hand grip strength and calculation of BMI.

Visit 5 (Day 90)

Patients have been fasting overnight.

Outpatient visit including collection of information about control of ascites (amount of ascites assessed using abdominal ultrasound and number of paracenteses since the last visit), adverse events and quality of life.

Collection of blood tests for standard biochemical analysis, measurement of weight and hand grip strength and calculation of BMI.

Visit 6 (Day 120)

Outpatient visit including collection of information about control of ascites (amount of ascites assessed using abdominal ultrasound and number of paracenteses since the last visit), adverse events and quality of life.

Collection of blood tests for standard biochemical analysis, measurement of weight and hand grip strength and calculation of BMI.

Visit 7 (Day 150)

Outpatient visit including collection of information about control of ascites (amount of ascites assessed using abdominal ultrasound and number of paracenteses since the last visit), adverse events and quality of life.

Collection of blood tests for standard biochemical analysis, measurement of weight and hand grip strength and calculation of BMI.

Visit 8 (Day 180; final assessment in the trial)

Patients have been fasting overnight.

Outpatient visit including collection of information about control of ascites (amount of ascites assessed using abdominal ultrasound and number of paracenteses since the last visit), adverse events and quality of life.

Collection of blood tests for standard biochemical analysis, measurement of weight and hand grip strength and calculation of BMI. The PleuX tunnelated catheter is removed if the subject decides that he/she would like the PleurX catheter removed after the final visit.

Unscheduled/Intermediate Visits

If patients are admitted between scheduled visits information about adverse events will be collected.

Medical device and labelling

The medical device tested is the PleurX tunnelated catheter (Pleurx Peritoneal Catheter System): CareFusion Pleurx Catheter Systems: K1 13854. The PleurX peritoneal catheter and sub devices relevant for the drainage procedure are listed in appendix: “Peritoneal Catheter Mini Kit Instructions for use_en”. Following precautions will be made when handling the medical device:

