Furthermore the listed parameters below occur regularly amongst patients with decompensated cirrhosis and ascites. They are thoroughly evaluated and afterwards categorized, by specialized hepatologists, as not being associated with carrying a permanent tunnelated peritoneal catheter. As a result this list of events will not be categorised at SAE but will be registered as AE:

- Hospitalisation du to large volume paracenthesis
- Alterations in type and dose of medicine
- Planned outpatient control visits due to other chronical diseases
- Hospitalisations due to chronic liver failure
- Hospitalisations due to alcohol intoxication
- Diagnosis of Hepatocellular carcinoma or other malignant diseases

Some side effects of ascites are obtained by letting the study participants answer the Quality of Life Questionnaire at every visit. Therefore these side effects will not also be listed as Adverse Events:

- Stomach pain or soreness
- Nausea
- Anorexia
- Reduced appetite
- Alterations in bowel habits
- Fatigue
- Dyspnoea
- Negative alterations in physical capability
- Leg pain

The type, potential relationship, severity, starts and end date for all AE must be recorded. The severity of the adverse event and the relationship with the study medical device must be assessed in accordance with the guidelines described below.

*The investigator must assess the relationship between an adverse event and the study medical device using the following guidelines:*

Adverse Device Effect (ADE): an adverse event related to the use of the medical device

Serious Adverse Event (SAE / pre-event): an event that results in i) death; ii) life-threatening injury or illness; iii) lasting harm to the body or bodily functions; iv) hospitalization or prolongation of existing hospitalization or required medical or surgical treatment are necessary to prevent i to iv.

Serious Adverse Device Effect (SADE): a serious incident which is related to the use of the medical device.

An almost-event is an equipment incident which does not have a serious output because of intervention before the event has evolved.

Serious incidents and near-incidents caused by improper treatment or error due to technical errors or defects in the equipment, instructions, labelling, use or maintenance of the equipment.

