Trial participants will be insured through the national patient insurance. Trial participants are informed of this relation in written information of trial participant’s rights, appendix 2. Sponsor and investigators are covered by their employment hospitals statutory insurance.

Finance and funding

PleurX catheters and drainage bottles will be purchased from Vingmed Danmark A/S. Drainage bottles for participants will be provided by Carefusion BD as a grant for device (up to 800 bottles). Carefusion BD does not provide financial support in addition to devices. Gastro Unit, medical division, Amager and Hvidovre Hospital will incur inpatient expenses during the trial.

Vingmed Danmark A/S is not further involved in the trial and has no influence whatsoever on the design and methodology, nor on compilation and publication of results.

Sponsor and initiator [name] has invented the overall template of this research project and has taken initiative to execute it. None of the involved investigators have economic or commercial conflicts regarding the investigations.

Investigators will be financed through clinical employments at their respective hospitals.

Expenses regarding trial investigations, admissions to hospital for the purpose of participating in the trial and extra outpatient visits will be undertaken by the involved hospitals.

Additional costs and expenses, including biochemical analyses and investigations will be covered through funds.

The trial has received grants from: University Hospital Hvidovre Research Foundation (2015; 84.000 Dkr.), Copenhagen University Internationalization Fund (2016; 120.000 Dkr.) and Hvidovre Hospitals Lægefond til bekæmpelse af Leversygdomme (2016; 30.000 Dkr).

PUBLICATION

The trial will be registered in clinical trial database www.clinicaltrials.gov before inclusion of the first patient. The results of the trial will be published in medical journals and conferences regardless of the results (positive, negative or inconclusive). We expect that the trial will lead to at least one publication. If we are unable to publish the result in a scientific journal, the results of the trial will be made public on www.clinicaltrials.gov.

LIST OF APPENDICES

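### Between visits, adverse events reach the record through hospital stays in one arm and home nurses in the other, so counts of non-serious events partly reflect who asks and how often

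*Protocol*

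**What the plan says.** Secondary outcome measures lists adverse events, and the synopsis states that neither patients, investigators nor outcome assessment can be blinded. Under Trial Flow, adverse events are collected in both arms on Days 0 and 1 and then at the visits on Days 30 to 180.

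Two routes are named for the time between visits.

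- Unscheduled/Intermediate Visits: "If patients are admitted between scheduled visits information about adverse events will be collected".
- Strategies for Recruitment and Retention: "We will collaborate with primary health care providers including at-home nurses in order to collect valid information about adverse events and other clinical outcomes".

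The Interventions section shows who has these contacts as a matter of routine. For paracentesis, "After the procedure, the patient remains in hospital for observation until the fluid is drained", and the Adverse Events section lists "Hospitalisation du to large volume paracenthesis" among expected events. For PleurX, "A home nurse will be trained in the drainage procedure and patient monitoring by specialised company staff from Vingmed", and "The home nurse will ensure that only a maximum of two litres of ascites fluid is removed at a time". No home nurse is described for the paracentesis arm.

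For each event, the Adverse Events section requires type, possible relationship, severity, and start and end dates. The source of the report is not among these items.

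**The concern.** Whether a mild or short-lived event is recorded depends on how soon someone asks and who that is. Here the routine between-visit observer is hospital staff in one arm and a home nurse in the other, and the number of contacts differs as well. The protocol sets no common between-visit enquiry, such as a telephone call or diary. In the visit descriptions, the period since the last visit is attached to the number of paracenteses and not clearly to adverse events, so the scheduled question is not explicitly tied to the whole interval.

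The stated objective is to weigh beneficial against harmful effects. With 16 patients per arm, a few extra minor events on one side can change how the harms comparison reads.

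**Working it through.** The protocol gives no figure on this point to reproduce. The check compares the routes by arm, counts routine contacts, and then asks how far unequal capture could move a ratio.

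**1. Routes by arm**

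| Route | PleurX | Paracentesis |
|---|---|---|
| Scheduled visits (Days 0, 1, 30, 60, 90, 120, 150, 180) | same | same |
| Interim admission | other causes only | other causes, plus stays for assigned paracentesis |
| Home nurse | described for drainage and monitoring | not described, though not excluded by the recruitment section |

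**2. Routine contacts over 180 days**

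- *Paracentesis.* Ethical considerations expects a need for paracentesis weekly, bimonthly or monthly. 180/7 gives about 25 contacts and 180/30 gives 6. If bimonthly means every two weeks, 180/14 gives about 12; if it means every two months, 180/60 gives 3. Some of these may coincide with scheduled visits, so they are upper figures for extra contact. They also assume that each procedure counts as an admission.
- *PleurX.* No frequency of nurse visits is stated. Assume the same volume is removed, 5 L per paracentesis and 2 L per drainage, with a nurse at each drainage. Then 25 × 5/2 ≈ 62, 12 × 5/2 = 30 and 6 × 5/2 = 15 contacts. As a rough cross-check, Finance and funding mentions up to 800 bottles: 800/16 = 50 per patient, or 50/(180/7) ≈ 1.9 a week if one bottle serves one drainage.

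Both arms therefore have an extra route, of unknown yield.

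**3. Effect on recorded counts at equal true risk**

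Let q be the share of events captured at scheduled visits and c the share of the remainder captured between visits. The recorded share is 1 − (1 − q)(1 − c). Both q and c are assumptions. One arm is given c = 0.5.

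| q | c = 0 in the other arm | c = 0.2 | c = 0.5 |
|---|---|---|---|
| 0.60 | 0.80/0.60 = 1.33 | 0.80/0.68 = 1.18 | 1.00 |
| 0.80 | 0.90/0.80 = 1.125 | 0.90/0.84 = 1.07 | 1.00 |
| 0.95 | 0.975/0.95 = 1.03 | 0.975/0.96 = 1.02 | 1.00 |

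The distortion shrinks as scheduled capture improves and vanishes if the two routes work equally well. The table does not say which arm has the better route, and neither does the protocol.

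**The case against.** The strongest reply is that the difference in setting is inherent in comparing home with hospital drainage, that scheduled enquiry is identical, and that every adverse event must be recorded. Several parts of this stand. The Adverse Events section moves pain, nausea, appetite loss, fatigue, dyspnoea and other symptoms to the questionnaire, which removes many of the events most sensitive to being asked. Much of what remains, such as infection, leakage or bleeding, leaves a clinical trace. The recruitment section does not confine nurses to PleurX, and admissions for other causes occur in both arms. The choice of events for the main comparison can also be left to the SAP. What the reply does not remove is that routine contacts follow allocation, and that the protocol does not ask for the source.

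Four stronger readings are tempting.

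- *A reader might infer a large loss of events in one arm.* Suppose the chance of reporting a minor event halves every h days. Mean capture at enquiry interval T is then (1 − 2^(−T/h))/((T/h) ln 2). For h = 7, 14 and 28 days it is 0.319, 0.521 and 0.706 at T = 30, and 0.541, 0.721 and 0.845 at T = 14. An arm with monthly enquiry only would lose 41%, 28% and 16% against an arm asked every 14 days. But neither arm is shown to rely on monthly visits. With 30 nurse contacts (T = 6; 0.754, 0.865, 0.929) against procedures every 14 days, the loss is 28%, 17% and 9%, and it falls on the paracentesis arm. Size and sign both follow from the assumption, so none of these figures estimates the bias.
- *A reader might infer that the bias could never be repaired.* Event dates are recorded, data are drawn from medical records, and monitors can see source documents, so part of the source could be reconstructed. The CRF is not shown and may already hold it.
- *A reader might infer that the supplier shapes the adverse-event data.* The protocol says its staff train nurses in drainage and monitoring, not in adverse-event reporting. The statement that "Vingmed Danmark A/S is not further involved in the trial" goes on to exclude influence on design, methodology and publication.
- *A reader might add that ascitic fluid is sampled on different schedules, or that paracentesis admissions are themselves registered as adverse events.* Both are separate matters and do not enlarge this one.

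**Conclusion.** The point holds in a limited form. Scheduled enquiry is equal, but the named between-visit routes differ by allocation for routine contacts, so the comparison of non-serious adverse events partly measures who asks and how often. The net direction cannot be determined from the document, and the two routes may partly cancel, although nothing in the protocol ensures that they do. The recorded ratios of 1.00 to 1.33 illustrate assumed capture rates and do not predict the bias. Deaths and serious events should be found in both arms and are little affected. The conclusion rests on reading a stay for assigned paracentesis as an admission at which adverse events are collected, and on nurses attending PleurX drainages with some regularity. It is worth correcting because harm is part of the objective and the correction is cheap.

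**What to change.** 1. Add a CRF field for the source of each adverse event: scheduled visit, interim admission, or home nurse or other provider.
2. At every scheduled visit, ask both arms the same standard question covering all events since the last visit.
3. Base the main between-arm comparison on events elicited at scheduled visits, plus deaths and serious events taken from records in the same way in both arms. Beside it, report the all-source comparison by arm and source as supportive, so that no device event first seen at home is dropped.

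Items 1 and 2 are data-collection rules and belong in the protocol and CRF. Item 3 may sit in the SAP. The cost is one CRF field, one standard question and one extra table, with no added visits. The downside is that some minor events count only in the supportive comparison. The fix reduces the imbalance without removing it, because an event already discussed at an earlier contact may be more readily recalled at the next visit.
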